#### Secondary outcomes

Quantitative variables will be compared between the two arms with a Mann-Whitney test. Categorical variables will be compared between the two arms with a chi-square test or a Fisher’s exact test as appropriate.

### Interim analysis {21b}

No interim analysis is planned.

### Methods for additional analyses {20b}

There is no plan to conduct any additional analyses.

### Methods in analysis to handle protocol non-adherence and any statistical methods to handle missing data {20c}

The trial will follow the modified intent to treat principle as defined above. Patients who withdraw consent before having received a dose of treatment will be excluded from statistical analysis. Those patients will be replaced if possible to conduct the statistical analysis on 22 patients, as planned in the sample size calculation. We will not exclude from analysis patients in case of intervention discontinuation and will follow the participants discontinuing the intervention during the study duration. Because of the ICU context, we expect no missing data on the primary outcome.

## Oversight and monitoring

### Composition of the coordinating center and trial steering committee {5d}

This is a single-center study, performed and coordinated in la Pitié-Salpêtrière University Hospital, Paris, France. Day-to-day support for the trial is provided by: the principal investigator (takes supervision of the trial and medical responsibility of the patients), the project manager (trial registration, visits) and the research coordinator (collection of baseline data and follow-up of the patients). The principal investigator and the research coordinator meet weekly.

The research group will act as a trial steering committee. Members of the committee are Pr [name] principal investigator, [name] [name] methodologist, and [name] and [name] URC project managers. The missien of the steering committed are to define the general organization of the research, to coordinate the information, to determine the methodology, to monitor the progress of the research, and to propose methodological adjustments during the course of the research. Members of the steering committee meet before the beginning of the study, three months after the inclusion of the first patient, at the end of recruitment, when the database is frozen, when statistical analyses are statistical analyses, and whenever necessary. The meetings will be face-to-face or by telephone if it is not possible to meet face-to-face.

### Composition of the data monitoring committee, its role, and reporting structure {21a}

Given the fact that this study involves a low-risk intervention, there is no data monitoring committee planned in this study.

### Adverse events reporting and harms {22}

In this study, an adverse event will be defined as any untoward medical occurrence in a patient without regard to the possibility of a causal relationship. The investigators will be responsible for collecting all adverse events in the eCRF based on those referred by the patient spontaneously or by an interview in the follow-up visits. The causality of the adverse event with the intervention will be evaluated and recorded in the medical record and in the eCRF.

The investigators will report to the sponsor all serious adverse events occurring to patients treated in the clinical trial, without undue delay but not later than within 24 h of obtaining knowledge of the events. The sponsor will report to the French Health Products Agency all relevant information about suspected unexpected serious adverse reactions to investigational medicinal products occurring in this clinical trial. Serious adverse events will be defined as events that (1) result in death, (2) are life-threatening, (3) requires prolongation of hospitalization, and (4) result in a significant or lasting disability or handicap.

In addition, the following non-serious adverse events will be of particular interest: nausea ≥grade 3, constipation ≥grade 4, bradypnea <12 per minute, confusion or delirium, drowsiness or even coma, defined by a Glasgow Coma Scale ≤9, pruritus grade ≥4, functional ileus, worsening of the respiratory condition requiring intubation.

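### Coma and intubation for respiratory worsening are labelled non-serious, in conflict with the same section's definition of a serious adverse event

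*Protocol article*

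**What the plan says.** All the conflicting text stands in one section of the protocol article, Adverse events reporting and harms {22}.

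- Definition: "Serious adverse events will be defined as events that (1) result in death, (2) are life-threatening, (3) requires prolongation of hospitalization". The fourth criterion is significant or lasting disability.
- Reporting duty: "The investigators will report to the sponsor all serious adverse events occurring to patients treated in the clinical trial", and this "not later than within 24 h of obtaining knowledge of the events". The sponsor in turn passes suspected unexpected serious reactions to the national agency.
- List: the next paragraph says that "the following non-serious adverse events will be of particular interest". Among the items are "drowsiness or even coma, defined by a Glasgow Coma Scale ≤9" and "worsening of the respiratory condition requiring intubation". The list has no reporting deadline of its own; like all adverse events, these go into the eCRF.

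Two other sections set the context. Composition of the data monitoring committee {21a} says that "there is no data monitoring committee planned in this study", on the ground that the intervention is low-risk. Interim analysis {21b} says "No interim analysis is planned".

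**The concern.** An opioid given to patients in acute respiratory failure who are not intubated has two obvious major harms: loss of consciousness, and respiratory deterioration that ends in intubation. The background section itself names fear of respiratory depression as the main historical obstacle to using morphine for dyspnea. These are the two harms that the plan puts under a non-serious label.

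Two things are at stake.

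- **Timeliness.** The 24-h duty attaches to serious events only. An investigator who follows the label could record a coma or an intubation in the eCRF and send no expedited report. The event would then not be considered for onward reporting to the agency either, since that step also covers serious reactions only. No monitoring committee or interim look would make up for the delay.
- **The final safety summary.** Serious events within 48 h are among the secondary outcomes. If some comas and intubations are filed as non-serious, that count is too low. Under blinding the same rule applies to both arms, so the undercount favours neither arm by design. It would still shrink any true difference between arms in that count.

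**Working it through.** There is no figure in the plan to reproduce on this point. The check is a comparison of text.

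**Step 1: what makes an event serious.** The section uses four criteria, all about consequence: death, threat to life, longer hospital stay, lasting disability. They are meant to be applied event by event, whatever the diagnosis.

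**Step 2: what the list does.** The list classifies by type of event. It names the events and calls them non-serious. It does not say that it covers only those instances that fail the four criteria.

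**Step 3: whether the listed events would meet a criterion.** Under Eligibility criteria {10}, patients breathe spontaneously, have a RASS between 0 and 2 and are not confused. Those already intubated, or with intubation planned on admission, are not included. A coma or an intubation during the trial is therefore a new and major deterioration in someone already in acute respiratory failure. It would ordinarily be life-threatening.

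**Step 4: the two rules side by side.**

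| Event | By the four criteria | By the list |
|---|---|---|
| Coma (GCS ≤9) | Ordinarily serious (life-threatening) | Non-serious |
| Respiratory worsening leading to intubation | Ordinarily serious (life-threatening) | Non-serious |
| Drowsiness, nausea, constipation, pruritus and the other items | Depends on the case | Non-serious |

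The first two rows conflict. The third need not: many such events will be non-serious by the criteria as well.

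**Step 5: what follows for reporting.** By the criteria, the first two rows go to the sponsor within 24 h. By the list, no deadline applies.

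**Step 6: what is collected anyway.** The secondary outcomes {12} include intubation, coma, impaired alertness (GCS ≤12) and delirium, each over 48 h. The Glasgow Coma Scale and CAM-ICU are recorded every 4 h for 48 h. The occurrence of these events reaches the database whatever label they carry.

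**Step 7: size.** The number of events affected depends on how often they occur, and the article gives no rate. As an assumption only, an intubation rate of 10% to 30% within 48 h would give 22 × 0.10 = 2.2 to 22 × 0.30 = 6.6 intubations among the 22 planned patients. That range counts events to which the label could apply. It does not count events that would be misfiled.

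**The case against.** The strongest defence is that the list begins as an addition to the serious-event rules. It can be read as asking for extra attention to these events when they do not meet a seriousness criterion. On that reading a life-threatening coma is still serious and still reported within 24 h. Part of this stands: no sentence exempts any event, and an investigator who applies the four criteria would report correctly. But the limiting condition is not in the text, which calls the events themselves non-serious. An investigator who follows the label would also be acting within the protocol as worded.

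A second defence is that an article condenses a fuller protocol. That would excuse a missing timeline for events of special interest, and no such omission is claimed here. It does not excuse a classification that the article states and that conflicts with its own definition.

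A reader might also infer three stronger points, which the document does not support.

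- *That these events are removed from 24-h reporting.* The text is contradictory; it does not forbid or waive the report.
- *That expedited reporting is the only way anyone outside the ICU would see a harm signal.* Sponsor-appointed research assistants make regular visits and compare the eCRF with source data {23}. A steering committee with a methodologist and project managers monitors progress and can meet whenever needed {5d}. These routes have no 24-h clock and do not replace a monitoring committee, but they exist.
- *That 2 to 7 patients would have their main harm misfiled.* That needs both an intubation rate the article does not give and the assumption that every case is filed as non-serious.

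Finally, intubation may reflect the course of the underlying disease. That bears on causality, which is assessed separately, and does not change whether the event is serious.

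**Conclusion.** The contradiction is real and lies within one section. Coma and intubation for respiratory worsening are called non-serious, although in these patients they would ordinarily meet the plan's own life-threatening criterion. That last step is a clinical presumption drawn from the eligibility criteria and is not stated in the article.

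The consequence is limited to how seriousness is classified and how fast the sponsor is told. Taken literally, the label could leave the two principal harms unexpedited and the serious-event count too low, with no monitoring committee and no interim analysis as a safeguard. Data capture, the primary analysis and the sample size are not affected. No number can be attached without assuming event rates and how investigators would file the events. The point does not depend on one, and it deserves correction because it concerns the harms that matter most here.

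**What to change.** In Adverse events reporting and harms {22}:

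1. Delete the word non-serious from the sentence that introduces the list, and call the items adverse events of special interest.
2. State that every listed event is classed by the seriousness criteria of the same section.
3. State that a coma or an intubation meeting a criterion, ordinarily the life-threatening one, is reported to the sponsor within 24 h like any other serious event.

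It is not necessary to declare all listed events serious. Drowsiness, nausea and the rest are left to the criteria. If the full protocol carries the same label, it needs the same change. The cost is a few words in the safety section and a few extra 24-h reports. Treatment, schedule, data collection and analysis stay as they are.

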### Frequency and plans for auditing trial conduct {23}

The sponsor appoints Clinical Research Assistants (CRA) who ensure that the trial is conducted in accordance with good clinical practice and who carry out regular monitoring visits to research locations. The CRA will check consent forms, compliance with the protocol and the planned procedures, quality of data collected in the eCRF, coherence of data collected with source data, and management of treatments used. The French authority in charge of health products, Agence nationale de sécurité du médicament et des produits de santé (ANSM) can audit the trial at its own discretion.

### Plans for communicating important protocol amendments to relevant parties (e.g. trial participants, ethical committees) {25}

Any modifications to the protocol that impact on the conduct of the study, potential benefit of the patient or may affect patient safety, including changes of study objectives, study design, patient population, sample sizes, study procedures, or significant administrative aspects will require a formal amendment to the protocol. Such amendment will be submitted to the South Mediterranean III Comité de Protection des Personnes Important protocol changes as well as changes in eligibility criteria, outcomes, or analyses will be communicated to the investigators, institutional ethics committee, trial participants, and trial registries.

### Dissemination plans {31a}

The results will be published in a journal of impact and in scientific congresses related to the subject of the study.

## Discussion

We expect this study to have a significant benefit to the patient. Relieving dyspnea should be a major therapeutic goal in ICU patients, as is pain management.

Dyspnea is a nociceptive sensation that shares many characteristics with pain. Patients exposed to dyspnea have reported terrifying experiences. With VAS scores of dyspnea ≥ 40, dyspnea can be described as “moderate to severe.” Similar pain scores would indicate an immediate analgesic response. In addition, patients with dyspnea are more likely to have anxiety than non-dyspnea patients, it is likely that dyspnea may contribute to the severe neuropsychological sequelae of resuscitation.

The expected short-term benefit would be to relieve patients by pharmacological means. The immediate gain for the patient would be the immediate disappearance of this nociceptive sensation, in the same way, that an analgesic treatment relieves pain. In the longer term, the benefit would be to reduce the prevalence and severity of neuropsychological sequelae such as post-traumatic stress disorder. This study will allow us to verify our hypothesis by looking for a signal of effectiveness and to show that a morphine titration protocol is feasible in these patients before the realization of a therapeutic trial of a larger scale.

## Trial status

The current version of the protocol is Version 4.0, of the 22 April.

The first patient included in the study occurred on 16 December 2020.

The recruitment period is 30 months (June 2023).

## Data Availability

The datasets used and/or analyzed during the current study will be available from the corresponding author on reasonable request.
